### Statistical methods

There is no prior published research outlining effectiveness of iCBT for treatment of a clinical depression or anxiety disorder in a cancer setting. In order to calculate sample size, data was taken from published randomised controlled trial of a transdiagnostic iCBT program [26]. Assuming the effect size of >0.6, and taking power at 80% with alpha set at 0.05%, sample size is calculated to be 44 per group. This is to detect a 0.6 effect size for the iCBT group to improve more than the treatment as usual group. Recruitment of 50 per group will be undertaken to account for attrition.

All analyses will be conducted at conclusion of the trial period, i.e. when all participants in the treatment group have completed the iCBT program. All analyses will be implemented in SPSS. Consideration will be given to the stratification into ‘active treatment’ and ‘post-treatment’.

Significance testing of group differences regarding demographic data and pre-treatment measurements will be conducted using analysis of variance (ANOVA) and *χ*2 where the variables consist of nominal (or categorical) data. Intent-to-treat (ITT) mixed models using restricted maximum likelihood (REML) estimation will be used to account for missing data due to participant drop-out. Mixed models do not assume that the last measurement is stable (the last observation carried forward assumption) [48, 49]. REML models are appropriate for RCTs with multiple time points and pre-to post-only designs [50]. The assumption that data are missing at random (MAR) will be evaluated using binary logistic regression to predict drop-out (0 = no drop-out, 1 = drop-out) and by comparing these two groups on baseline measures. Significant effects will be followed up with pairwise contrasts comparing mean pre-treatment to mean post-treatment scores. Mediation analyses will be used to examine the association between change in depression and anxiety symptoms over treatment and change in each of FCRI and FACT-G in separate analyses. Tests of the indirect effects (mediation) will be conducted using PROCESS [51].

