**Methods/design:**

Early stage cancer survivors will be recruited via the research arm of a not-for-profit clinical research unit and randomised to an intervention (iCBT) group or a ‘treatment as usual’ (TAU) control group. The minimum sample size for each group is 45 people (assuming effect size > 0.6, power of 80%, and alpha at .05), but 10% more will be recruited to account for attrition. A solitary or cumulative diagnosis(es) of Major Depressive Episode (current), Generalised Anxiety Disorder, Illness Anxiety Disorder, Panic Disorder, Agoraphobia, and/or Adjustment disorder will be determined using modules from the Anxiety Disorders Interview Schedule for DSM-5. Depression and anxiety levels with be measured via the total score of the Hospital Anxiety and Depression scale (HADS-T), the primary outcome measure. Secondary measures will include the Kessler 10 to measure general distress, the Fear of Cancer Recurrence Inventory (FCRI) to measure the specific fear of cancer recurrence and the Functional Assessment of Cancer Therapy, General Version 4 (FACT-G) for self-report of physical, social, emotional and functional well-being. iCBT participants will complete the measures before lessons 1 and 5, at post-treatment and at 3-month follow-up. The TAU group will complete similar measures at weeks 1, 8 and 16 of the waiting period. Program efficacy will be determined using intent-to-treat mixed models. Maintenance of gains will be assessed at 3-month follow-up. Mediation analyses using PROCESS will be used to examine the association between change in depressive and anxious symptoms over time and changes in FCRI and FACT-G QOL in separate analysis.

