### Randomisation

Accepted participants will be stratified according to their phase in their cancer experience into the ‘active treatment’ group and ‘post-treatment’ group as described earlier. Thereafter, they will be randomised based on an allocation sequence generated by an independent person not involved in the study via a true randomisation process (www.random.org). Numbers corresponding to treatment group (1 = iCBT) or the treatment as usual group (2 = TAU) will be placed in sealed opaque envelopes bearing the sequential order number to ensure participant allocation based on the pre-determined randomisation sequence. A member of the research team will open the envelope after the diagnostic interview.

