### Trial procedure

Figure 1: Participant Flow Chart details the time line for participants in the study. Once randomised, participants will be allocated to either the iCBT arm or the TAU arm. Over the sixteen week period, both groups undertake the same set of measures three times, the start, mid-point and end of the intervention. In the iCBT group, these times will vary according to when the participant undertakes the specific lesson; whereas for the TAU group, the questionnaires are according to specific times (i.e. weeks since commencement of group). Administration time points for measures are contained in Table 1. Baseline records of psychotropic medications and whether they are accessing psychological support will be captured for participants in both groups. Participants will be asked to inform the research team if any of their current interventions change.

**Table 1 Tab1:** Administration time points for questionnaires used in the RCT

Measure	Pre-treatment^a^	Before each lesson^b^	Mid –treatment^c^	Post-treatment^d^	3-month follow-up^b^
HADS-T	♦		♦	♦	♦
K-10	♦	♦	♦	♦	♦
PHQ9-Q9	♦		♦	♦	♦
BDI-II Item 9	♦		♦	♦	♦
FCRI	♦		♦	♦	♦
FACT-G	♦		♦	♦	♦
CEQ	♦			♦	
ADIS	♦				♦

*HADS-T* Hospital Anxiety and Depression Scale,Total score, *K-10* Kessler-10 Psychological Distress Scale, *PHQ9-Q9* Patient Health Questionnaire 9-itme scale, Question 9, *BDI-II Item 9* Beck Depression Inventory-II, Item 9, *FCRI* Fear of Cancer Recurrence Inventory, *FACT-G* Functional Assessment of Cancer Therapy – General, *CEQ* Credibility and Expectancy/Satisfaction Questionnaire, *ADIS* Anxiety Disorders Interview Schedule for DSM-5

^a^iCBT group pre Lesson 1; TAU group at week 1 (Baseline)

^b^iCBT group only

^c^iCBT group pre Lesson 5; TAU group at week 8

^d^ iCBT group post Lesson 8; TAU group at week 16 (End)

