### Description of the interventions

#### Internet delivered CBT (iCBT), the ‘iCanADAPT Early’ program group

The ‘iCanADAPT Early’ Program is a self-managed, 16 week online cognitive-behavioural intervention consisting of eight lessons involving general CBT skills and then cancer-specific CBT skills. Content is presented in the form of an illustrated comic-based storyboard in which two animated characters gain mastery over their anxiety and depressive symptoms with the help of a clinician. The female character is currently undergoing cancer treatment and tackling clinical levels of depression, while the male character is post-treatment with predominant anxiety symptoms. The participant follows both characters journeys to recovery across the 8 lessons. The *title*, and expansion of the main focus of each lesson are in Table 2: Course overview.

**Table 2 Tab2:** Course overview

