### Measures

#### Primary outcome measure

### Hospital anxiety and depression scale, total score (HADS-T)

The primary endpoint is anxiety and depression severity at post treatment as measured by the Hospital Anxiety and Depression Scale Total score (HADS-T) [35]. The HADS was developed as an outcome measure to assess anxiety and depression that avoids reliance on the measurement of somatic symptoms (e.g., fatigue, or insomnia) that may be experienced by people with cancer as part of the presenting illness. HADS-T is a fourteen item self-report questionnaire divided into two sub-scales, HADS-D, depression subscale and HADS-A, an anxiety subscale. The HADS-T is the total HADS score and is the combined score of the depressive and anxiety sub-scales. High scores indicate greater morbidity. This validated measure is widely used in clinical settings and has been validated in cancer patients [29].

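### All analyses are timed to the iCBT arm finishing the program, which cuts short the planned 3-month follow-up analysis and is not tied to the last TAU week-16 scores

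*Protocol article*

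**What the plan says.** The Statistical methods section sets a single trigger: "All analyses will be conducted at conclusion of the trial period, i.e. when all participants in the treatment group have completed the iCBT program". The Randomisation section gives code 1, the treatment group, to iCBT and code 2 to TAU, so the trigger looks at one arm only.

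The abstract plans a later analysis: "Maintenance of gains will be assessed at 3-month follow-up". It also gives the iCBT schedule: "iCBT participants will complete the measures before lessons 1 and 5, at post-treatment and at 3-month follow-up". Table 1 lists HADS-T, K-10, FCRI, FACT-G and the ADIS interview at that follow-up, and its footnote limits the follow-up to the iCBT group.

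The primary endpoint is the post-treatment HADS-T score. Table 1 places it after Lesson 8 in iCBT and at week 16 in TAU. The Trial procedure section says of the iCBT assessments: "In the iCBT group, these times will vary according to when the participant undertakes the specific lesson". The program is described as a "self-managed, 16 week online cognitive-behavioural intervention consisting of eight lessons".

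The Trial status section reports first enrolment on 1 March 2016 and schedules data analysis for late 2017. No section sets a later cut for follow-up data or links the cut to TAU week 16.

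**The concern.** The rule covers all analyses, but one planned analysis needs data that arise about 13 weeks after the event named. Followed exactly, the 3-month result would describe earlier finishers and omit the last ones.

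The same rule ignores the control arm. The primary comparison needs a week-16 TAU score. If the last people enrolled are in TAU, or the last iCBT participants finish their lessons early, some TAU scores are not yet due when the trigger is met. They would be missing only because of the cut date and, unless flagged, could be counted as drop-outs in the planned logistic regression of drop-out.

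Finally, the word for completion is not defined for people who stop early. The plan expects such people: it adds 10% for attrition, allows fewer than eight lessons, and models missing data from drop-out.

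**Working it through.** **The plan's own figure.** The effect size is 0.6, power 80% and two-sided alpha 0.05 (the abstract's value). The normal approximation gives n = 2 × (1.960 + 0.842)² / 0.6² = 43.6, so 44 per group. The t-based calculation gives 44.6, so 45. Allowing for 10% attrition, 45 / 0.9 = 50. The sample size therefore reproduces, and the timing point does not depend on it.

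**Order of events for one late iCBT participant.** Lesson 8 is finished, the post-treatment measures are taken, the trigger is met, and the 3-month follow-up comes about 13 weeks later. The conflict for the latest finishers needs no assumption. Only its size does.

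**Share without follow-up at the trigger.** Assume even entry of 50 iCBT participants over 52 to 78 weeks, and a cut made when the trigger is met.
- Entry per arm: 50/78 = 0.64 to 50/52 = 0.96 per week.
- Over 13 weeks: 8.3 to 12.5 participants, or 13/78 = 17% to 13/52 = 25%.
- A simulation with random uniform entry over an assumed 26 to 65 weeks gives about 20% to 52%. The share is larger when recruitment is faster.

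**TAU scores outstanding at the trigger.**
- If iCBT takes exactly 16 weeks, the last entrant is equally likely to be in either arm. The simulation agrees: at least one TAU score falls after the trigger in about 49% to 51% of runs. The expected number is small: each of 50 TAU participants has a chance of 1/51 of entering after all 50 iCBT participants, so 50/51, about one person.
- If iCBT takes 8 to 16 weeks (assumed), at least one TAU score falls after the trigger in about 88% to 94% of runs.
- If the last iCBT participants finish 4 to 6 weeks early (assumed), 0.64 × 4 = 2.6 to 0.96 × 6 = 5.8 TAU participants are outstanding, or 5% to 12% of 50.

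**Power.** Two-sample t-test, d = 0.6, two-sided 5%:

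| iCBT v TAU | Power |
|---|---|
| 45 v 45 | 80.4% |
| 45 v 42 | 79.0% |
| 45 v 39 | 77.4% |

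These figures overstate the loss. They subtract people from the 45 evaluable as if none of them would otherwise have dropped out, and they ignore the baseline and week-8 TAU scores that the planned mixed model keeps.

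**Calendar.** Counting from 1 March 2016:
- 12 months of entry puts the last week-16 score at about 20 June 2017 and the last follow-up at about 19 September 2017.
- 18 months puts them at about 21 December 2017 and 22 March 2018.
- For 16 + 13 = 29 weeks to end between 30 September and 31 December 2017, the last entry must be by about 11 March to 11 June 2017.

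**The case against.** The strongest reply is the late-2017 date. With about 12 months of recruitment, both the last TAU score and the last follow-up would be in before analysis starts, and nothing says that data are cut on the day the trigger is met. This stands as a reason to expect a smaller shortfall in practice. But a calendar target does not replace the event that the plan names, and it stops protecting the follow-up if recruitment runs long.

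A second reply is that data-cut rules are usually left to a full protocol or analysis plan. That would answer a complaint that the rule is missing. Here a rule is stated, and it conflicts with another stated analysis.

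Three stronger readings are tempting, and the documents do not support them:
- *No follow-up data would exist.* Earlier finishers would already have theirs, so the data would be incomplete and not absent.
- *The trigger can never be met.* Taken literally, with 10% attrition, the chance that all 50 complete is 0.9^50 = 0.5%. But the same section plans an intention-to-treat analysis that allows for drop-out, so the authors evidently mean to analyse with drop-outs present. Completion may simply mean that the 16-week program period has ended. What remains is that the wording does not say so.
- *The primary comparison is biased, or staff choose the cut knowing the results.* Scores missing because of entry date are not thereby related to outcome. Allocation is open, but no interim look is described.

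**Conclusion.** Wrong as written, with minor to moderate severity. The firm part is the conflict between one trigger for all analyses and a planned follow-up about 13 weeks later. It affects an uncontrolled, iCBT-only analysis and leaves the randomised comparison untouched. Its size, about 17% to 25% of the iCBT arm, rests on assumed even entry over 12 to 18 months and a cut at the trigger.

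The TAU part is a possibility and not a prediction. It depends on entry order, lesson pace and an immediate cut. Even on unfavourable assumptions, power falls by at most about 3 percentage points (80.4% to 77.4%). The undefined completion term is a matter of wording.

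**What to change.** Replace the sentence with two data cuts:
1. Run the between-arm primary and secondary analyses once the last randomised participant in either arm has passed the post-treatment or week-16 assessment window. State when that window closes for iCBT, and state that the cut does not depend on how many lessons were completed.
2. Run the 3-month iCBT follow-up analysis once the last iCBT participant's follow-up window has closed.

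This changes wording only and leaves the sample size, measures and visits as they are. The cost is a wait of perhaps a few weeks for the primary analysis and about 3 months for the follow-up analysis. If the late-2017 date already allows for both, there may be no delay. Aligning the two arms' assessment times would not replace this change, because it would leave the follow-up conflict and the undefined completion term in place.

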## Discussion

This RCT will evaluate the efficacy of an iCBT intervention for clinical depression and/or anxiety in people with early stage cancer going through treatment or post-treatment. As the majority of e-health interventions in psycho-oncology to date focus on supportive care [17], this is a novel program as it will evaluate iCBT in clinical depression and/or anxiety. Fortunately, cancer survivors have an overall “positive attitude” to self-management and e-Health [52].

If proven efficacious, and acceptable to patients, the iCBT intervention would be added to the armoury of psychological treatments offered to cancer survivors suffering from anxiety and depression symptoms generally. It will be a core component of the forthcoming ADAPT Cluster Randomized Controlled trial. Moorey [53] importantly asked in 2013 “*I know they are distressed, what do I do now?”.*, He outlines that, despite many advances in Psycho-Oncology, services need to incorporate less labour intensive methods of delivery of therapy (primarily CBT), in order to be widely accessible and sustainable. He proposed that internet therapy will have a role in the changing interface of how care is provided in the cancer setting. This trial will add to the research aiming to address the short fall he outlines. It will add to recent work on the role of online interventions in other areas of supportive care, such as fatigue and acute distress [54], for people living with, or survivors of cancer. As an RCT aiming to recruit over 100 participants, it will add to the literature base and build on the pilot and feasibility studies in this area of psycho-oncology. Furthermore this trial will add to the growing literature of the use of iCBT for treating emotional health problems in patients with a co-morbid physical illness.

Online, or internet, interventions are easy to access, including in rural areas, accessible by the user at any time, private and confidential, self-empowering, scalable and cost-effective and can meet the needs of most patients, freeing staff to see only the most severe cases [11]. As Mitchell [55] pointed out “*screening is generally ineffective without aftercare*”; hopefully iCBT can become a viable, evidence-based treatment option in the future, thereby increasing treatment afforded to patients screening positive for distress and depression.

### Trial status

Trial registration: Australian New Zealand Clinical Trials Registry: ACTRN12616000231448, registered 19^th^ February 2016 (www.anzctr.org.au). This trial protocol is in compliance with the Standard Protocol Items: Recommendations for Interventional Trials (SPIRIT) guidelines. The first patient was enrolled 01^st^ March 2016. Data analysis is scheduled for late 2017.
